## Abstract

Endometrial cancer is a leading gynecological malignancy, with obesity being a significant risk factor due to increased estrogen production in body fat. Current treatments often involve hysterectomy, which precludes fertility, thus highlighting the need for fertility-preserving options. This study aims to evaluate the combined efficacy of a levonorgestrel intrauterine device (LNG-IUD), metformin, and liraglutide for treating women with endometrial hyperplasia or early stage endometrial cancer while preserving fertility. The study will enroll 264 women aged 18–45 with a BMI > 30 who desire uterine preservation. Participants will be randomized into three groups: LNG-IUD alone, LNG-IUD plus metformin, and LNG-IUD plus metformin and liraglutide. Primary outcomes will include complete pathological remission, while secondary outcomes will assess histological changes, glucose, insulin levels, and weight changes over a 12-month period. This study protocol hypothesizes that LNG-IUD combined with metformin and liraglutide may potentially lead to higher regression rates of endometrial hyperplasia (EH) and early stage endometrial cancer (EC) compared to LNG-IUD alone. Furthermore, the protocol anticipates that these combination therapies will demonstrate good tolerability with minimal adverse effects, suggesting the potential benefit of integrating metabolic interventions with LNG-IUD to enhance treatment efficacy while preserving fertility in women with EH and EC.

## 1. Introduction

Endometrial cancer (EC) stands as a prevalent concern in developed societies, ranking as the most common gynecological cancer globally and the sixth most common overall [1,2]. Estimations project a potential 50% surge in global cases by 2040, highlighting the urgency to redefine its management [3]. The estrogen dependence of 70–80% of EC types links to the presence of aromatase in body fat, fostering heightened estrogen production with increased body fat levels. This notably elevates the risk of EC, with women categorized as obese or severely obese facing 2.6 to 4.7 times higher likelihoods of developing the disease compared to those with normal weight [4,5].

Even in the early stages, conventional therapy involves the removal of the uterus, fallopian tubes, and sentinel lymph nodes; and, in some cases, systematic lymph node dissection. However, this approach excludes future fertility prospects impacting around 14% of premenopausal women, including 5% younger than 40 years old [5]. Therefore, the demand for fertility-preserving therapies is markedly amplified [6], although these methods mean a diversion from standard guidelines, which needs a holistic, multidisciplinary approach in every single patient’s case [7,8]. When deciding about fertility sparing, it is crucial that the desire for childbearing and reproductive capability are still present despite the diagnosis.

To address this critical need, the concept of using progesterone preparations, particularly intrauterine devices (IUDs) containing LNG-levonorgestrel, gained traction. These devices ensure continuous progesterone release within the uterine cavity, offering a more favorable side effect profile compared to oral progesterone formulations [9]. Simultaneously, recognizing the imperative to mitigate excess estrogen dominance, aggressive weight-loss therapy emerges as an essential adjunct to reduce tumorous growth. 

Metformin and Glucagon-like peptide-1 (GLP-1) agonists, which have been attracting increasing attention lately, offer promising approaches for reducing the risk of endometrial cancer by impacting molecular and metabolic pathways. Metformin, by activating AMP-activated protein kinase (AMPK) and inhibiting the mTOR pathway, can suppress cell proliferation and induce apoptosis in endometrial cancer cells [10,11]. Additionally, metformin’s ability to improve insulin sensitivity and reduce insulin levels addresses metabolic dysregulation, a key driver of endometrial cancer [12]. 

GLP-1 agonists exhibit antitumor effects by inhibiting inflammatory processes, which are significant because chronic inflammation is linked to the development and progression of various cancers. Additionally, GLP-1 agonists activate intracellular cAMP pathways, leading to cell cycle arrest and the inhibition of cell proliferation and tissue invasion, thereby counteracting cancer cell growth and metastasis [13,14]. Furthermore, GLP-1 agonists’ impact on weight loss and metabolic parameters offers an additional layer of protection against endometrial cancer development in high-risk populations. Combined, these medications could present a multifaceted approach to reduce the risk of endometrial cancer by targeting both molecular and metabolic pathways involved in its pathogenesis [15].

While studies have explored the role of LNG-IUDs in managing early stage endometrial cancer and hyperplasia, there is a noticeable gap in research concerning the impact of metabolic intervention [16]. This underscores the necessity for additional investigations to understand how the combination of weight loss and LNG-IUDs affects the complete pathological response rate, emphasizing the need for further exploration of fertility preservation and tumor regression. This will be the first investigation to examine the role of liraglutide in such a patient group. 

Our overarching goal is to investigate the combined impact of progesterone preparations, metformin, and liraglutide-based weight loss therapy on patients with hyperplasia or early stage endometrial cancer. This approach aims to not only counterbalance estrogen dominance but also preserve fertility in affected individuals, paving the way for a novel, comprehensive treatment strategy in this population. One of our specific aims is to determine the combined effect of LNG-IUD, metformin, and liraglutide, and to assess the differences in their effectiveness. We aim to investigate whether metformin alone, or in combination with liraglutide, is more effective alongside the standard LNG-IUD treatment in achieving complete pathological remission.

Another key aim is to investigate the metabolic impact of these treatments and their relation to complete pathological remission. We will monitor glucose and insulin levels, as well as track weight loss (measured in kilograms) at set intervals during the 12-month check-up. This comprehensive assessment seeks to deeply understand how interventions interact with metabolic reactions, offering valuable insights into their influence on both physiological indicators and tangible results.

## 2. Experimental Design

This protocol was developed following the guidelines outlined in the Standard Protocol Recommendations for Interventional Trials (SPIRIT) reporting template [17]. This multi-center randomized 1:1:1 open-label clinical trial has three treatment groups: LNG-IUD, LNG-IUD plus metformin and LNG-IUD plus metformin and liraglutide therapy. The study protocol was approved and registered by the Ethics Committee of Semmelweis University (SE RKEB 63/2024). 

### 2.1. Study Setting

The study will involve women aged 18–45 diagnosed with endometrial hyperplasia or early stage endometrial cancer who meet the following criteria: (1) desire to retain their uterus and (2) obesity (BMI > 30). Early stage endometrial cancer criteria include stage 1, grade 1 disease with no lymphovascular space invasion and no myometrial invasion, as diagnosed by ultrasound or MRI. We plan to enroll 264 patients between January 2025 and December 2025.

### 2.2. Eligibility Criteria

#### 2.2.1. Inclusion Criteria

Women in their reproductive years (18–45);sup>∙ Females with a body mass index (BMI) > 30 kg/m^2^;Histologically confirmed EHA or low-grade endometrioid endometrial cancer;No sign of myometrial invasion (confirmed by a gynecologist oncologist ultrasound or MRI—FIGO IA);No hypersensitivity or contraindications to LNG-IUD, MA, or metformin, or liraglutide;No use of metformin before inclusion at least for 2 years;Understanding the study design, risks and benefits, providing informed consent, and the ability to comply with the study protocol;Negative pregnancy test 7 days before starting the treatment.

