#### 2.2.2. Exclusion Criteria

Previous treatment for endometrial cancer;Advanced endometrial cancer (FIGO IA<);Non-endometrioid, or high-grade histology;Known allergies or intolerances to LNG-IUD, or diabetic medications;Inability to comply (exercise and attend on regular visits);Disorders other than diabetic endocrine disorders (renal disorder, liver failure);Lactation;Previous thrombosis, stroke, or acute myocardial infarction in the anamnesis.

Clinical characterization includes not only demographic information and clinical observation but also laboratory and histology testing. Enrolled patients undergo hysteroscopy to sample the entire endometrium. Women who had previously undergone dilatation and curettage (D&C) for this diagnosis were not required to undergo a second sampling, but the previous pathology specimen should be obtained by an expert gynecologic pathologist. 

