## 3. Procedures

### 3.1. Intervention

The levonorgestrel intrauterine device has been approved as a standard therapy in case of fertility-sparing procedures [20]. Compared to systematic progesterone therapy, adverse effects do not include nausea, thromboembolic complication, or weight gain [21].

A combination of 3000 mg (or maximum tolerated dose) of metformin will be administered to the study participants. To avoid gastrointestinal side effects such as diarrhea, bloating, and stomach pain, the metformin dose will be administered less rapidly, but reach the final dose within 2 months [22]. 

Liraglutide, a long-acting GLP-1 agonist, will be administered via subcutaneous injection once daily, irrespective of mealtimes or time of day. To enhance gastrointestinal tolerability, an initial dose of 0.6 mg will be used. After a minimum of one week, this dose should be escalated to 1.2 mg. For certain patients, further titration up to the maximum recommended dose of 1.8 mg daily may be beneficial [23].

Since all the patients in this trial will have a BMI over 30 kg/m^2^, medication of all three groups will include 2 × 2 g of Inositol, a diet plan comprising 160–200 g of carbohydrates, and a daily exercise routine of 40–60 min of walking. Exercise levels (sedentary, moderately active, and sufficiently active) will be measured using the Active Australia Survey [24].

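### Eligibility sets a 2-year metformin-free period but no parallel rule for GLP-1 receptor agonists, so women who keep taking one could dilute the liraglutide contrast

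*Protocol article*

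**What the plan says.** The inclusion list (Protocol article, section 2.2.1) protects one of the two added drugs against earlier exposure: "No use of metformin before inclusion at least for 2 years". The other added drug, liraglutide, appears in that list only in a safety criterion: "No hypersensitivity or contraindications to LNG-IUD, MA, or metformin, or liraglutide". The exclusion list (section 2.2.2) refers to antidiabetic drugs only in terms of tolerance, "Known allergies or intolerances to LNG-IUD, or diabetic medications", and its only treatment-history item is "Previous treatment for endometrial cancer".

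Two further criteria describe who may enter. All participants must satisfy "Females with a body mass index (BMI) > 30 kg/m^2". The comorbidity exclusion reads "Disorders other than diabetic endocrine disorders (renal disorder, liver failure", which leaves women with diabetes eligible.

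Section 3.1 identifies the drug class given only in arm C: "Liraglutide, a long-acting GLP-1 agonist, will be administered via subcutaneous injection once daily". The Introduction makes the contrast between B and C a specific aim: "We aim to investigate whether metformin alone, or in combination with liraglutide, is more effective alongside the standard LNG-IUD treatment". Section 2.3 includes the role of liraglutide in the primary objective.

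**The concern.** The metformin criterion shows that the authors saw prior exposure to a study drug as a threat to the comparison. The same reasoning applies to liraglutide, yet nothing in the printed lists limits use of it or of another drug in its class. Followed as written, they admit a woman who is taking a GLP-1 receptor agonist on the day of randomisation.

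Two things are at stake:

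- **Remission.** A woman in arm A or B who continues the drug receives part of what arm C is meant to add. The A versus C and B versus C differences both shrink towards zero. B versus C suffers most directly, because liraglutide is all that separates those arms.
- **Metabolic secondary outcomes.** Weight, glucose and insulin are followed as changes over 12 months (section 2.3.2). A woman already on the drug starts from values that it has already shifted. This applies in all three arms, including C, where the added liraglutide would appear to do less than it does in an untreated woman.

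**Working it through.** **1. Does any other text close the gap?** The criteria that mention liraglutide or diabetic medications concern hypersensitivity, contraindication, allergy or intolerance. None concerns use. Two other places hint at untreated entry: section 3.6 has diabetic medication begin at baseline, and section 3.1 describes a starting dose with later escalation. Both describe what arm C receives. Neither bars a current user, and neither applies to arms A and B. The gap stands.

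**2. The protocol's own sample size (section 2.5).** Inputs: A 58.9%, B and C 86.7% each, α = 0.05, three-group chi-square test (2 df), 33 per group.

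- Mean rate = (0.589 + 0.867 + 0.867)/3 = 0.7743.
- Noncentrality = n·Σ(pᵢ − mean)²/[mean·(1 − mean)] = 9.73 at n = 33.
- Power is 0.804 at n = 33 and 0.791 at n = 32, so 33 reproduces.
- Dropout: 33/(1 − 0.24) = 43.4, rounded up to 44. Then 44 × 3 arms × 2 diagnoses = 264.

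No stated figure is in dispute. With 80.4% power, the design has almost no margin above its 80% target.

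**3. Dilution of B versus C (illustrative).** The planning rates put B and C both at 86.7%, so they contain no difference to dilute and one has to be assumed.

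Assumptions: B 70% without exposure; C 86.7%; a share f of arm B continues a GLP-1 agonist and responds at the arm C rate; both diagnoses pooled, so 33 × 2 = 66 per arm.

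Observed B = 0.70 + f × 0.167, so the difference becomes (1 − f) × 16.7 points. Power is Φ{[d − 1.96·SE₀]/SE₁}, with SE₀ from the pooled rate and SE₁ from the two separate rates. At f = 0: d = 0.167, SE₀ = 0.0717, SE₁ = 0.0702, giving Φ(0.377) = 0.647.

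| f in arm B | Observed B | Difference (points) | Power, 66 per arm |
|---|---|---|---|
| 0 | 70.0% | 16.7 | 65% |
| 5% | 70.8% | 15.9 | 61% |
| 10% | 71.7% | 15.0 | 57% |
| 20% | 73.3% | 13.4 | 48% |

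**4. Dilution of the planned three-group test at 33 per group, 10% exposure in arm A.** With B and C both planned at 86.7%, only arm A can be diluted here. Two assumptions bracket the effect:

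- Exposed women in A reach the full arm C rate: A = 0.589 + 0.10 × 0.278 = 0.6168, noncentrality 8.12, power 0.724.
- Exposed women in A gain only the 16.7 points assumed in step 3, since they take no metformin: A = 0.589 + 0.10 × 0.167 = 0.6057, noncentrality 8.75, power 0.758.

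Power therefore falls from 80% to about 72–76%.

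**The case against.** The strongest reply is that the protocol leans towards untreated entry and that exposure may be rare. Starting diabetic medication at baseline, escalating liraglutide from an initial dose and requiring no contraindication to it all fit a woman new to the class. An investigator might also turn a current user away on her own judgement. In addition, an eligible woman with diabetes must have been off metformin for two years, which narrows that subgroup. The document gives no prevalence of GLP-1 agonist use. At 1% exposure the B versus C power in the illustration moves only from 65% to 64%.

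Most of this stands as a limit on size. It does not remove the gap: hints are not a criterion, and centres could apply them differently.

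Four stronger readings are tempting, and the documents do not support them.

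- **Imbalance or bias between arms.** Randomisation (section 3.2) spreads such women over all three arms, so no imbalance is expected.
- **Harm from any past use.** Dilution needs continued use. A woman who has stopped contributes little.
- **A large pairwise A versus C loss.** Giving exposed women in A the full arm C rate credits them with a metformin effect that they do not receive. It also tends to overstate the drug's effect, since a current user has the disease at entry despite taking it.
- **A missing plan to record non-trial drugs.** A condensed article may leave this to the full protocol, so its absence here is no finding.

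It is also fair to say that with B and C planned at the same rate, the B versus C contrast has no planned power even without dilution. That is a separate matter. It means that the illustration rests on an assumed difference, not on the protocol's own.

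**Conclusion.** The point holds in a limited form. The printed eligibility lists protect the metformin contrast and leave the liraglutide contrast unprotected. This is uneven within the criteria as stated, so it is not a detail deferred to an analysis plan. The consequence is dilution towards no difference by women who continue a GLP-1 agonist in arm A or B, together with baseline metabolic values already shifted by the drug in all arms.

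The size is unknown. On the stated assumptions, 5–20% exposure costs B versus C between 4 and 16 percentage points of power (from 65% to 61–48%). With 10% exposure in arm A, the planned three-group test falls to about 72–76%, below its 80% target. The exposure shares, the 70% rate in B, the pooling to 66 per arm and the response of exposed women are all assumptions. The figures show that modest exposure would matter; they do not show that it will occur. The point merits correction because the remedy is cheap and the contrast is one of the trial's stated aims.

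**What to change.** Add to section 2.2.1 a criterion on GLP-1 receptor agonist use before inclusion, parallel to the metformin criterion, with the look-back period set by the sponsor. It should be worded so that it clearly covers women taking such a drug at screening.

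The cost is one eligibility line and the exclusion of a few otherwise eligible women. The sample size figures of 33, 44 and 264 do not change.

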#### 2.2.2. Exclusion Criteria

Previous treatment for endometrial cancer;Advanced endometrial cancer (FIGO IA<);Non-endometrioid, or high-grade histology;Known allergies or intolerances to LNG-IUD, or diabetic medications;Inability to comply (exercise and attend on regular visits);Disorders other than diabetic endocrine disorders (renal disorder, liver failure);Lactation;Previous thrombosis, stroke, or acute myocardial infarction in the anamnesis.

Clinical characterization includes not only demographic information and clinical observation but also laboratory and histology testing. Enrolled patients undergo hysteroscopy to sample the entire endometrium. Women who had previously undergone dilatation and curettage (D&C) for this diagnosis were not required to undergo a second sampling, but the previous pathology specimen should be obtained by an expert gynecologic pathologist. 

### 2.3. Objectives

The primary objective of this study is to assess the efficacy of combined progesterone containing IUD and combines metformin and liraglutide therapy to achieve the complete pathology response rate histological results and define the role of metformin and liraglutide in the pathological response. To provide a thorough analysis, we will monitor glucose and insulin levels, and track weight loss over a 12-month period. This comprehensive assessment is designed to explore how these interventions interact with metabolic processes, thereby offering valuable insights into their impact on both physiological markers and overall health outcomes.

#### 2.3.1. Primary Outcome

The primary outcome is the complete pathological remission of endometrial hyperplasia or early stage endometrial cancer in response to the therapy of LNG-IUD plus metformin and combined with liraglutide. 

#### 2.3.2. Secondary Outcome

The secondary outcomes include:

Assessing histological changes compared to baseline after 3 months;

Assessing histological changes compared to baseline after 6 months;

Assessing histological changes compared to baseline after 9 months;

Monitoring changes in glucose and insulin levels during the 12-month checkup;

Tracking weight changes during the 12-month checkup;

Comparing the effectiveness between study groups.

### 2.4. Study Assessments and Procedures 

The study assessments and procedures performed at baseline and at 3-, 6-, 9-, and 12-month visits are summarized in Table 1.

### 2.5. Sample Size

For both endometrium hyperplasia and endometrial cancer groups, a parallel, 3-group design will be used to assess whether there is any difference in the rates between the groups. The two-sided hypotheses will be evaluated with the chi-square test, with an overall Type I error rate (α) of 0.05. For the sample size calculations, the response rate for arm A (LNG-IUD) is expected to be 58.9%, while the response rates for both arms B and C (LNG-IUD plus metformin and LNG-IUD plus metformin plus liraglutide) are expected to be 86.7% based on the results of [18]. To reach at least 80% power with equal group size, the sample size needed is 33/group. Additionally, 24% of the participants are expected to be drop out [19], resulting in an increased target sample size of 44 participants/group (total sample size = 264).

### 2.6. Statistical Methods

Where applicable, baseline participant characteristics will be presented as frequencies and proportions (%) for categorical data and the mean, standard deviation, median and interquartile range (IQR) for continuous data. As the study interventions are considered low-risk interventions, no interim analysis is planned. The statistical tests for the primary outcome variable will be two-tailed, and a value of *p* < 0.05 will be considered to indicate statistical significance. All analyses will be performed using R version 4.4.1.

### 2.7. Provision of Study Materials

The LNG-IUDs will be supplied by Richter Gedeon PLC, while all diabetic medications will be manufactured by Novo Nordisk and provided through their generosity for this study.

### 2.8. Recruitment

Patients meeting the eligibility criteria will be recruited from gynecological oncology centers, coordinated by Semmelweis University, Hungary. Detailed information about the study will be provided verbally and in writing by the examining physician.

### 2.9. Implementation

The principal investigator or a designated sub-investigator will input the required data into the web-based allocation system for eligible patients. Subsequently, the system will allocate participants to either the LNG or LNG + metformin or LNG + metformin + liraglutide group. 

## 3. Procedures

### 3.1. Intervention

The levonorgestrel intrauterine device has been approved as a standard therapy in case of fertility-sparing procedures [20]. Compared to systematic progesterone therapy, adverse effects do not include nausea, thromboembolic complication, or weight gain [21].

A combination of 3000 mg (or maximum tolerated dose) of metformin will be administered to the study participants. To avoid gastrointestinal side effects such as diarrhea, bloating, and stomach pain, the metformin dose will be administered less rapidly, but reach the final dose within 2 months [22]. 

Liraglutide, a long-acting GLP-1 agonist, will be administered via subcutaneous injection once daily, irrespective of mealtimes or time of day. To enhance gastrointestinal tolerability, an initial dose of 0.6 mg will be used. After a minimum of one week, this dose should be escalated to 1.2 mg. For certain patients, further titration up to the maximum recommended dose of 1.8 mg daily may be beneficial [23].

Since all the patients in this trial will have a BMI over 30 kg/m^2^, medication of all three groups will include 2 × 2 g of Inositol, a diet plan comprising 160–200 g of carbohydrates, and a daily exercise routine of 40–60 min of walking. Exercise levels (sedentary, moderately active, and sufficiently active) will be measured using the Active Australia Survey [24].

